### 2.3. Randomization and Allocation Masking

Participants are assigned to their treatment group (ratio 1:1) following a computer-generated random sequence. The latter is generated by a lab technician otherwise not involved in the trial. It is transferred to individual cards, which are inserted into opaque, sealed, consecutively numbered envelopes. When the participant signs the consent form and eligibility is confirmed, the first sealed envelope is opened to reveal the treatment group, and the patient is scheduled for the baseline assessment tests and the eight fortnightly sessions.

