### 2.7. Outcomes

The primary outcome is the change in body weight between the start of the programme and the time of surgery.

Secondary outcomes include: changes in body composition, comorbidities, changes in eating behaviours, health-related quality of life, functional capacity, length of hospital stay after surgery and short-term complications of surgery.

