### 2.9. Body Composition

Body composition is assessed at the baseline visit. Weight is assessed with a calibrated bioimpedance (*Tanita BC 420 MA III*, Tokyo, Japan) to the nearest 0.1 kg, and height, using a stadiometer to the nearest 0.5 cm, without shoes and with light clothing. Body Mass Index (BMI) is then calculated as weight (in kg) divided by height (in meters)^2^. Body composition is analyzed through Vectorial Bioimpedance by tetrapolar impedance plethysmography using an electric alternating current flux of 400 µA at an operating single sinusoidal frequency of 50 kHz (*Nutrilab™*, Akern, Firenze, Italy in resting conditions. Standard whole-body measurements are performed according to the manufacturer’s guidelines on the right side of the body with the subjects in supine position with their arms and legs abducted, and the skin cleaned to ensure good contact. The thighs are checked not to be in contact with each other and the arms not to be touching the sides of the body. Electrodes are placed on a line between the radial and ulnar styloid processes on the dorsum of the wrist and on a line between the medial and lateral malleoli on the dorsum of the ipsilateral foot, overlying the head of the third metacarpal on the dorsum of the hand and the third metatarsal on the dorsum of the foot. Total body water, fat-free mass, fat-free mass percentage, fat mass, fat mass percentage and body cell mass are determined according to the formulas of Kotler et al. [48], and bioelectrical parameters of resistance, reactance, and phase angle are registered.

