### 2.15. Statistical Analyses

At the time of the design of the protocol, we estimated that, during one year, we would be able to include 80 participants, 40 in each treatment arm, following two 10 person groups (one control and one intervention) at a time. The inclusion of 80 participants, without any loss to follow-up, assuming a standard deviation in weight of 11 kg [16], for a two-tailed *p* < 0.05, would allow a difference between groups, with 80–90% statistical power, of 8 and 7 kg to be detected, respectively. Assuming a standard deviation of 6 kg, as shown by other studies [64], the detectable difference would be reduced to around 4 kg.

A baseline descriptive analysis is performed, and variables are expressed as percentages, mean (SD) or median (interquartile range), as appropriate according to their type and distribution. Treatment groups are compared using chi-squared, Student’s *t* or Mann–Whitney’s *U*. Analyses will be performed by intention to treat. Missing values will be imputed using the last observation carried forward.

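### Section 2.15 names only unadjusted tests for comparing the arms; adjusting for baseline weight would give a modest gain in precision at essentially no cost

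*Protocol article*

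**What the plan says.** On the endpoint, section 2.7 states: "The primary outcome is the change in body weight between the start of the programme and the time of surgery". It is therefore a change score.

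On the comparison, section 2.15 states: "Treatment groups are compared using chi-squared", Student's t or Mann–Whitney's U, by intention to treat. No regression model, ANCOVA or covariate appears anywhere in the article.

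On the baseline value, section 2.9 states: "Body composition is assessed at the baseline visit". Weight is part of that assessment, recorded to 0.1 kg.

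On allocation, section 2.3 states: "Participants are assigned to their treatment group (ratio 1:1) following a computer-generated random sequence". No stratification by weight or BMI is described.

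On size, section 2.15 plans "80 participants, 40 in each treatment arm", "without any loss to follow-up", and expresses the target as a difference between groups in kg. It gives two scenarios: "assuming a standard deviation in weight of 11 kg" and "Assuming a standard deviation of 6 kg, as shown by other studies".

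**The concern.** Candidates for bariatric surgery differ widely in weight at entry. If kilograms lost depend on starting weight, two things follow for an unadjusted test on change. Part of the outcome variation that baseline weight could explain stays in the error term. And if one arm happens to start heavier, part of that difference carries into the estimated effect. In a trial of 80 without stratification by weight, adjustment for a value already on file is an inexpensive protection against both.

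The list of tests raises a further point. The sample size is built on a mean difference in kg. If Mann–Whitney were the test used for the primary outcome, the result would not be in that unit.

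**Working it through.** **Inputs.** From section 2.15: 40 per arm, two-sided 0.05, SD 11 or 6 kg. I read both as SDs of change, because raw weight in Table 2 varies about twice as much as 11 kg. From Table 2 (pilot): baseline weight 112.9 (SD 19.5) kg in 7 intervention patients and 135.9 (SD 23.2) kg in 8 controls. The correlation of baseline weight with final weight or with change is not given, so two assumptions are tried.

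**1. The plan's own figures.** Detectable difference = (1.960 + z for power) × SD × √(2/40).
- SD 11: 2.802 × 11 × 0.2236 = 6.89 kg at 80% power; 3.242 × 11 × 0.2236 = 7.97 kg at 90%.
- SD 6: 3.76 kg at 80%; 4.35 kg at 90%.

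The values 7, 8 and about 4 kg are reproduced for an unadjusted comparison of means. The article prints 8 before 7 against 80–90% power, which is the reverse of the correct pairing. That is a separate matter and does not affect this point.

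**2. Chance imbalance in baseline weight.** Pooled SD = √[(6 × 19.5² + 7 × 23.2²)/13] = 21.6 kg. With 40 per arm, SE = 21.6 × √(2/40) = 4.8 kg, and the 95% range is ±1.96 × 4.8 = about ±9.5 kg. The pilot gap is 135.9 − 112.9 = 23.0 kg, with SE 21.6 × √(1/7 + 1/8) = 11.2 kg, so about 2 SE there. It would be 23.0/4.8 = about 4.8 SE at 40 per arm.

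**3. Assumption A: equal SD of weight at both times.** Let ρ be the correlation of baseline and final weight. Then:
- ρ = 1 − SD(change)²/(2 × SD(baseline)²)
- share of an imbalance left in the unadjusted change difference = 1 − ρ
- variance with ANCOVA ÷ variance of change = (1 + ρ)/2

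| SD of change | Baseline SD | ρ | Variance factor | Detectable difference, 80% | Shift from a 1.96 SE imbalance |
|---|---|---|---|---|---|
| 11 | 19.5 | 0.841 | 0.920 | 6.61 kg | 1.36 kg |
| 11 | 21.6 | 0.870 | 0.935 | 6.66 kg | 1.23 kg |
| 11 | 23.2 | 0.888 | 0.944 | 6.69 kg | 1.14 kg |
| 6 | 19.5 | 0.953 | 0.976 | 3.71 kg | 0.40 kg |
| 6 | 21.6 | 0.961 | 0.981 | 3.72 kg | 0.37 kg |
| 6 | 23.2 | 0.967 | 0.983 | 3.73 kg | 0.34 kg |

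Each shift is (1 − ρ) × 1.96 × baseline SD × √(2/40). At SD 11, variance falls about 6–8% and power at 7 kg rises from 81.2% to 83.4–84.3%. At SD 6, variance falls about 2% and power at 4 kg rises from 84.6% to 85.2–85.5%.

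**4. Assumption B: change depends on baseline by 0.05–0.10 kg per kg.** The correlation is r = slope × SD(baseline)/SD(change), and the variance falls by r². At SD 11, r = 0.05 × 21.6/11 = 0.10 to 0.10 × 21.6/11 = 0.20, so variance falls 1–4%. An imbalance of 9.5 kg then shifts the result by 0.5–0.9 kg. The same slopes at SD 6 would give r = 0.18–0.36 and a fall of 3–13%, which shows how far the answer depends on the unknown correlation.

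**The case against.** The strongest reply is that nothing here is an error. Under 1:1 randomisation an unadjusted t-test is unbiased with a valid type I error, and its standard error already allows for chance imbalance. This stands: the point is efficiency, not validity.

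It can also be said that the sentence on tests is generic, follows the sentence on baseline description, and leaves covariates to an analysis plan that is not shown. This stands only in part. The article does name tests, and those named are unadjusted. If the sentence covered baseline comparisons alone, no test for the primary outcome would be stated, and the same addition would be useful.

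Three stronger readings are tempting, and the article does not support them.
- *The trial would leave an imbalance like the pilot's 23 kg uncorrected.* The endpoint is already a change score, so only part of an imbalance remains. Under assumption A even 23 kg would leave 2.6–3.7 kg at SD 11, or 0.8–1.1 kg at SD 6. A gap from 7 versus 8 patients is not a plausible size at 40 per arm.
- *Adjustment would cut variance by as much as 25%.* That needs a baseline–change correlation of 0.5. At SD 11 this means a slope of 0.5 × 11/21.6 = about 0.25 kg per kg, for which the article gives no basis.
- *The primary test will be picked after seeing the data.* The remark about type and distribution in section 2.15 concerns how variables are expressed. It does not describe a data-driven choice of test.

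**Conclusion.** The point holds as a free improvement. Section 2.15 names only unadjusted tests, although a relevant baseline value is collected in everyone and no stratification by weight is described. The stated test is valid but gives up some precision and leaves a small part of any chance imbalance in the estimate. If Mann–Whitney were used for the primary outcome, it would not yield the difference in kg on which the trial is sized.

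The size is modest. Under equal SDs the variance falls about 6–8% at SD 11 and about 2% at SD 6. Under a slope of 0.05–0.10 kg per kg at SD 11 it falls 1–4%. A chance imbalance at the edge of its 95% range shifts the unadjusted difference by about 0.3–1.4 kg. These figures rest on a baseline SD from 15 pilot patients, on full follow-up of 40 per arm, and on assumptions about a correlation that the article does not report.

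**What to change.** In section 2.15, name as the primary analysis an ANCOVA of weight at surgery (or of change in weight) on treatment arm and baseline weight. Report the adjusted difference in kg with its 95% CI. The two forms give the same treatment estimate once baseline weight is in the model.

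Use the same baseline-adjusted form for continuous secondary outcomes that are measured at baseline. The gain there may be larger: if the baseline–follow-up correlation were 0.5 (an assumption), the factor (1 + 0.5)/2 = 0.75 would mean 25% less variance than a change score. Keep Mann–Whitney as a sensitivity analysis only.

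The cost is a few sentences of text and one degree of freedom. No new data are needed. The main trial has not started, and the Discussion says that other protocol changes will go to the Ethics Committee, so this wording can go with them.

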### 2.10. Questionnaires

A series of self-completed questionnaires are completed before the first group session and after the last one. General health-related quality of life is assessed using the Spanish version of EuroQol-5D-5L (EQ-5D-5L) [49]. Dietary habits are explored using the Adherence to the Mediterranean Diet Adherence Screener (MEDAS) questionnaire [50], eating disorders, by means of the Spanish version of the Eating Disorder Inventory (EDI-3) [51,52], and anxiety and depression, using the Spanish version of the Hospital Anxiety and Depression Scale (HADS) [53,54].

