## 3. Results

Participants in the pilot study had their first visit between 8 August 2019 and 13 September 2019, and the interventions took place between October 2019 and January 2020. 

Out of the 51 patients on the waiting list, expected to be operated on at least 4 months after recruitment, 19 accepted to participate. The main reasons given for declining were participation in preoperative groups in another centre (on a different island), distance to the training site and schedule problems, mainly due to working hours. None of the patients refused to participate or was excluded due to linguistic barriers. A total of 15 (14 women) attended the first visit and were randomized. Their mean age was 40.0 ± 10.0 years, baseline BMI, 46.7 ± 5.9 kg/m^2^, and waist circumference 134.2 ± 12.0 cm. The most frequent complications of obesity were OSA (54%), osteoarticular disorders (40%), asthma (33.3%), hypertension (33.3%), infertility (35.7%), chronic venous insufficiency (28.6%), diabetes (26.7%), and dyslipidaemia (26.7%). Seven patients were randomized to the intervention group and 8 to the control group. Their baseline features are displayed in Table 2.

The first eight sessions took place between October 2019 and January 2020. Three participants dropped out before even starting the intervention (one travelled abroad, another one said the timing of the sessions was inconvenient, and the third did not give a specific reason). The rest attended between one and six sessions. Only five participants completed follow-up, three in the intervention and two in the control group. Of the ten patients not completing the programme, seven interrupted it due to early surgery. Unlike what was initially planned, because of the low attendance at the sessions, we decided to merge both treatment groups from session 2, since group intervention was not possible otherwise. The control group left after the standard session finished, whereas the intervention group joined the physiotherapist team thereafter.

The five participants completing the follow-up lost an average of 0.54 ± 5.2 kg (Intervention group +1.6 ± 4.3 kg; Control group −3.8 ± 5.7 kg) and the final BMI was 48.1 ± 7.6 kg/m^2^ (Intervention Group 45 ± 7.3 kg/m^2^; Control group 52.69 ± 10.6 kg/m^2^). Given the small sample size, no statistical analysis was performed and no conclusions can be drawn.

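### Carrying the last observation forward will usually impute little or no weight change, so it shrinks any true difference and counts carried values as data

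*Protocol article*

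**What the plan says.** Section 2.15 commits to intention to treat ("Analyses will be performed by intention to treat") and follows it with the only missing-data method in the article: "Missing values will be imputed using the last observation carried forward". The sentence is not limited to particular outcomes, so it covers the primary one. Section 2.7 defines that outcome: "The primary outcome is the change in body weight between the start of the programme and the time of surgery".

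The measurement schedule decides what can be carried forward. Weighing is described in section 2.9, which opens: "Body composition is assessed at the baseline visit". No interim weighing is named. On questionnaires, section 2.10 says: "A series of self-completed questionnaires are completed before the first group session and after the last one".

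On the pilot, the Results section reports: "Only five participants completed follow-up, three in the intervention and two in the control group". Seven had been randomised to intervention and eight to control. Of the ten who did not complete the programme, seven stopped because surgery came early, and three left before starting. The sample size in section 2.15 assumes no loss. The Discussion plans measures on adherence and timing but does not return to the missing-data rule.

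**The concern.** Last observation carried forward assumes that weight stays where it was when the participant was last weighed. In a trial of weight change that assumption contradicts the question being asked. If the last weight is the baseline weight, the imputed change is exactly zero. If an interim weight exists, the imputed change is a truncated one. For a questionnaire taken only twice, a missing second value always becomes a change of zero.

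Two consequences follow in either arm. A real difference is diluted in proportion to the share imputed. The imputed values also have little or no spread and are counted as observations, so the standard error is smaller than the data support. If one arm has more imputed values and both arms are losing weight, the arms also differ through missingness alone. The primary estimate would then partly reflect attendance and the timing of surgery.

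**Working it through.** **Inputs from the protocol article.** 40 per arm, two-sided 5%, Student's t, SD 6 kg with a detectable difference of about 4 kg (section 2.15). Pilot non-completion 4/7 = 57% intervention, 6/8 = 75% control, 10/15 = 67% overall. Non-completion for reasons other than early surgery 3/15 = 20% (Results).

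**Assumptions, not in the article.** Controls lose 5 kg on average. Loss is unrelated to outcome within arm. A carried value is a fraction f of the participant's final change. Two cases bound the result:
- baseline only: f = 0;
- mixed: 30% of those missing have f = 0 and the rest have f uniform on 0–0.75, so mean f = 0.7 × 0.375 = 0.2625.

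**Plan's own figure.** Detectable difference = (1.960 + z) × SD × √(2/40). At SD 6 this gives 2.802 × 1.342 = 3.8 kg at 80% power and 3.242 × 1.342 = 4.3 kg at 90%, so about 4 kg reproduces. At SD 11 the formula gives 6.9 and 8.0 kg. The article prints that pair in the reverse order, which is a separate matter.

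**Shrinkage with equal loss m.** Expected estimate = true difference × [(1 − m) + m × f]. For a true 4 kg:
- m = 20%: 4 × 0.80 = 3.2 kg (baseline only); 4 × 0.8525 = 3.4 kg (mixed).
- m = 67%: 4 × 0.333 = 1.3 kg (baseline only); 4 × 0.508 = 2.0 kg (mixed).

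**Interval and power.** Simulation, 20,000 trials per scenario, true difference 4 kg:

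| Equal loss | Carried-forward estimate | 95% CI coverage | Mean SE, carried forward | SE, observed weights only | Power, carried forward | Power, observed only |
|---|---|---|---|---|---|---|
| 20% | 3.2–3.4 kg | 91–93% | about 1.3–1.4 kg | about 1.5 kg | 63–73% | about 75% |
| 67% | 1.3–2.0 kg | about 33–56% | about 1.1 kg | about 2.4 kg | about 22–45% | about 37% |

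Power without any loss is 84%. Observed-only estimates stay at about 4 kg, as they must when loss is unrelated to outcome.

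**No true difference, unequal loss.** Expected bias = common mean change × (loss in control − loss in intervention) × (1 − f).
- 57% v 75%, common loss 5 kg: −5 × 0.179 × (1 − f) = −0.89 kg (baseline only) or −0.66 kg (mixed), apparently favouring intervention. Rejection is about 16% and 10%.
- Loss rates swapped between arms: same size, opposite sign.
- 10% v 30%, common loss 5 kg: −1.0 or −0.74 kg. Rejection is about 9–13%.
- 57% v 75%, common loss 0.54 kg (the mean in pilot completers): −0.10 or −0.07 kg. Rejection is about 5%.
- Equal loss of 20% or 67%, common loss 5 kg: bias zero, rejection about 5%.

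**The case against.** Four stronger readings are tempting, and the article supports none of them.

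*Two thirds of the primary outcomes will be missing.* The Results section says that ten did not complete the programme, not that ten lacked a weight at surgery. For the seven operated on early, the endpoint of section 2.7 came sooner, and their weight may be obtainable. It is equally true that the surgical data listed in section 2.14 do not include weight, and that pilot weight change is reported only for the five completers. The share missing is unknown. The Discussion's plans to recruit further down the waiting list and coordinate with the surgeons may lower it.

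*The rule inflates type I error.* It does so only with unequal loss and a material common weight change together. The pilot split of 4/7 against 6/8 is compatible with chance (Fisher's exact p = 0.61). The 5 kg common loss is an assumption, and at the pilot's 0.54 kg the inflation disappears.

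*The rule halves the power.* Most of the fall at 67% loss comes from the lost data: observed weights alone give about 37%, inside the carried-forward range of about 22–45%.

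*The rule favours a particular arm.* The direction depends on which arm loses more participants and on whether weight is falling. Pilot intervention completers gained 1.6 kg on average, and the article itself draws no conclusions from the pilot.

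It can also be said that the choice of method belongs in an analysis plan that is not shown. That would answer a missing detail, but here the article states a rule. The shrinkage and the understated standard error need neither unequal loss nor a common trend, so that part of the concern stands.

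**Conclusion.** The point holds in limited form. As written, the rule biases a true difference towards zero when loss is similar in the two arms, and it overstates precision. Under the stated assumptions a 4 kg difference loses 0.6–0.8 kg at 20% loss, with coverage only a little below nominal. At 67% loss it loses 2.0–2.7 kg and the interval is unreliable. Which end applies depends mainly on how many weights at surgery are recovered. False-positive rates of about 9–16% are possible but conditional, and the article does not show that those conditions will arise. Nor can the rule be defended as reliably conservative, because the sign of the bias can go either way. This should be fixed before the trial starts; it does not invalidate the design.

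**What to change.** Delete the carried-forward sentence from section 2.15 and replace it with the following.

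1. The weight recorded at surgery is used for every operated participant, in the arm assigned, whether or not the programme was completed. Add weight to the surgical data listed in section 2.14.
2. Weights still missing are handled by multiple imputation within arm, using baseline weight, BMI, sex and sessions attended. A baseline-adjusted analysis of observed weights, valid under missing at random, would serve nearly as well. With no interim weights named, a repeated-measures model would add little to the observed final weights.
3. One sensitivity analysis shifts the imputed weights by a range of fixed amounts (delta adjustment), including different shifts by arm.
4. Questionnaires are handled in the same way.

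The cost is a change of wording, collection of one item at surgery and a little more programming. Confidence intervals will be wider, but they will reflect the information actually collected. The main trial has not started, and the Discussion already foresees submitting protocol changes to the Ethics Committee, so this can go with them. None of it restores the power lost through missing weights; only recovering the weights does that.

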## 3. Results

Participants in the pilot study had their first visit between 8 August 2019 and 13 September 2019, and the interventions took place between October 2019 and January 2020. 

Out of the 51 patients on the waiting list, expected to be operated on at least 4 months after recruitment, 19 accepted to participate. The main reasons given for declining were participation in preoperative groups in another centre (on a different island), distance to the training site and schedule problems, mainly due to working hours. None of the patients refused to participate or was excluded due to linguistic barriers. A total of 15 (14 women) attended the first visit and were randomized. Their mean age was 40.0 ± 10.0 years, baseline BMI, 46.7 ± 5.9 kg/m^2^, and waist circumference 134.2 ± 12.0 cm. The most frequent complications of obesity were OSA (54%), osteoarticular disorders (40%), asthma (33.3%), hypertension (33.3%), infertility (35.7%), chronic venous insufficiency (28.6%), diabetes (26.7%), and dyslipidaemia (26.7%). Seven patients were randomized to the intervention group and 8 to the control group. Their baseline features are displayed in Table 2.

The first eight sessions took place between October 2019 and January 2020. Three participants dropped out before even starting the intervention (one travelled abroad, another one said the timing of the sessions was inconvenient, and the third did not give a specific reason). The rest attended between one and six sessions. Only five participants completed follow-up, three in the intervention and two in the control group. Of the ten patients not completing the programme, seven interrupted it due to early surgery. Unlike what was initially planned, because of the low attendance at the sessions, we decided to merge both treatment groups from session 2, since group intervention was not possible otherwise. The control group left after the standard session finished, whereas the intervention group joined the physiotherapist team thereafter.

The five participants completing the follow-up lost an average of 0.54 ± 5.2 kg (Intervention group +1.6 ± 4.3 kg; Control group −3.8 ± 5.7 kg) and the final BMI was 48.1 ± 7.6 kg/m^2^ (Intervention Group 45 ± 7.3 kg/m^2^; Control group 52.69 ± 10.6 kg/m^2^). Given the small sample size, no statistical analysis was performed and no conclusions can be drawn.

